#### Eligibility criteria

2.6.1

Eligible participants must meet all of the following criteria: age 18–75 years; Eastern Cooperative Oncology Group performance status (ECOG PS) of 0–1; Child–Pugh class A or B7 (score 5–7); prior radical hepatic resection at a participating center; and histopathological confirmation of HCC. All participants must undergo hepatic angiography 4–8 weeks postoperatively, demonstrating no intrahepatic tumor staining. Additional requirements include no prior systemic antitumor therapy for HCC, adequate organ and bone marrow function, and an estimated life expectancy greater than 6 months. Participants must present with at least one high-risk recurrence factor, including tumor rupture, maximum tumor diameter > 5 cm, multifocal disease, microvascular invasion on postoperative pathology, Vp1/Vp2 portal vein invasion, lymph node metastasis confirmed by postoperative pathology, positive or narrow surgical margins, or Edmondson grade III–IV differentiation. Participants must be capable of understanding study procedures and providing written informed consent. Women of childbearing potential must confirm absence of pregnancy and, where applicable, all participants must use highly effective contraception (annual failure rate < 1%) for at least 120 days following hepatic angiography.

#### Exclusion criteria

2.6.2

Participants will be excluded if they lack pathological confirmation of HCC or have a history of other malignancies within 5 years prior to enrollment. Additional exclusion criteria include a history of hepatic encephalopathy, liver transplantation, or clinically significant pleural effusion, ascites, or pericardial effusion after curative hepatectomy. Participants with a history of drug allergy, active pulmonary tuberculosis, active syphilis infection, autoimmune disease, or long-term glucocorticoid use will also be excluded. Further exclusions include severe infection within 4 weeks prior to the first intervention or prior receipt of systemic antitumor therapy. Pregnant or lactating women are not eligible. Participants unable to adhere to the treatment protocol or complete follow-up will also be excluded.

#### Criteria for discontinuation

2.6.3

Participants may discontinue study treatment or be withdrawn prematurely under the following conditions: initiation of antitumor therapy other than adjuvant TACE or antiviral therapy for hepatitis B or C after curative hepatectomy, including but not limited to anti-angiogenic tyrosine kinase inhibitors or immune checkpoint inhibitors; disease progression requiring modification of treatment strategy; occurrence of SAEs or intolerance to the study intervention (all SAEs and adverse events will remain included in safety analyses); withdrawal of consent by the participant; investigator-determined discontinuation for medical reasons; inadequate compliance with study requirements; confirmed pregnancy, which will also be reported as an SAE; use of prohibited concomitant medications or substances that may affect safety or efficacy assessments; development of a condition that substantially alters clinical status or study endpoints; diagnosis of a second primary malignancy; or death.

### Strategies to improve adherence to interventions

2.7

The interventions employed align with established clinical practice. Participants in the adjuvant TACE group will receive treatment in accordance with CNLC recommendations,^29^ facilitating early detection of residual disease. Participants in the intensive follow-up group will avoid unnecessary treatment-related costs and potential adverse effects. The study will be conducted in accordance with GCP and applicable ethical standards. Investigators will maintain consistent and thorough communication with participants to promote adherence, reduce loss to follow-up, and minimize missing data. Prior to enrollment, investigators will provide a detailed explanation of study procedures, potential benefits, associated risks, and participant rights, including the right to withdraw consent at any time without consequence. Enrollment will proceed only after written informed consent has been obtained.

All analyses will follow the intention-to-treat principle. Participants who discontinue treatment or withdraw from the study prior to completion of the protocol-specified regimen will be encouraged to continue follow-up and complete all scheduled assessments. At the time of discontinuation or withdrawal, all end-of-treatment evaluations will be performed. For participants who withdraw for reasons other than disease progression, imaging assessments will remain mandatory.

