#### Sequence generation

2.9.1

Randomization will be performed using computer-generated random number tables managed by Good Clinical Practice-compliant research centers at participating sites. Personnel responsible for sequence generation will have no involvement in study conduct. The interval between randomization and administration of adjuvant TACE will not exceed 1 week. During angiography, if tumor staining is identified in the remnant liver, TACE will be performed for clinical management; however, such participants will be excluded from the study.

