### Sample size calculation

2.12

Sample size estimation was performed using PASS 2021 (version 21.0.3) for a noninferiority randomized controlled trial. Based on historical data from our center, the median RFS for patients with high-risk recurrence factors managed with intensive follow-up alone was 16.1 months,^13^ corresponding to a hazard rate of 0.043 (ln(2)/16.1). Enrollment is planned over 1 year, followed by at least 2 years of follow-up. With a one-sided α of 0.025, 80% power, and a 1:1 allocation ratio, 192 participants per group (total *n* = 384) are required to demonstrate noninferiority at a hazard ratio margin of 1.4, with an estimated 139 events per group. Assuming an annual attrition rate of 5%, an additional 58 participants are required, yielding a total sample size of 442.

Sensitivity analysis was conducted using an alternative median RFS of 19.0 months derived from a cohort excluding DSA-positive patients,^34^ corresponding to a hazard rate of 0.0365 (ln(2)/19.0). Under similar assumptions, 360 and 361 participants would be required in the experimental and control groups, respectively (total *n* = 721), to achieve 80% power at the same noninferiority margin. Given the practical constraints of an investigator-initiated study without commercial funding, enrollment of more than 700 participants is not feasible; therefore, a target sample size of at least 442 participants has been selected to ensure study reliability.

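### If a claim is made against the 1.4 noninferiority margin, the rule that every analysis follows intention-to-treat leaves it without a per-protocol check

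*Protocol article*

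**What the plan says.** Four parts of the protocol article bear on this.

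- **Analysis set (2.7, the section on adherence).** "All analyses will follow the intention-to-treat principle". The sentence has no exception, and no per-protocol or as-treated efficacy analysis appears elsewhere in the article.
- **Sizing (2.12).** The calculation is "for a noninferiority randomized controlled trial". "With a one-sided α of 0.025, 80% power, and a 1:1 allocation ratio", the stated numbers "are required to demonstrate noninferiority at a hazard ratio margin of 1.4, with an estimated 139 events per group". Neither the main calculation nor its sensitivity version gives a superiority effect size.
- **Question and test (2.1 and 2.13).** The primary objective asks whether adjuvant TACE improves RFS. Section 2.13 declares a one-sided superiority framework at α 0.05. No noninferiority test or decision rule is written down, and no arm is named as the one to be shown noninferior.
- **Departures (2.9.1 and 2.6.3).** "The interval between randomization and administration of adjuvant TACE will not exceed 1 week". The discontinuation criteria list other antitumor therapy, inadequate compliance and "use of prohibited concomitant medications or substances that may affect safety or efficacy assessments".

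**The concern.** In a superiority trial, departures from allocated treatment usually shrink the observed difference, so ITT works against the sponsor's claim. In a noninferiority trial the same shrinkage helps the claim. Suppose the arms truly differ by the full margin. TACE patients who go untreated, or off-protocol antitumor treatment before recurrence that narrows the gap between arms, then bring the ITT hazard ratio closer to 1, and the upper confidence limit falls below 1.4 more often than it should.

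A per-protocol analysis is the usual way to see whether a noninferiority result comes from similar managements or from similar exposure. An article may leave the definition of such a set to the analysis plan. Here, however, a rule is stated, and read literally it excludes the check. At stake is the one-sided 2.5% error on which the sample size in 2.12 is built.

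**Working it through.** **Inputs from 2.12:** margin 1.4; one-sided α 0.025; power 80%; 1:1 allocation; median RFS 16.1 months; 12 months' accrual plus 24 months' follow-up; 192 per group; 139 events per group (278 in all). **Assumed, because the article does not say:** true HR 1 for the sizing; intensive follow-up is the arm to be shown noninferior; all departure rates.

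**Step 1: reproduce the plan's size.**

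- Events = 4(z₀.₉₇₅ + z₀.₈₀)² / (ln 1.4)² = 4 × 7.849 / 0.11321 = 277.3, rounded up to 278.
- Monthly hazard λ = ln 2 / 16.1 = 0.04305. Event probability = 1 − [exp(−24λ) − exp(−36λ)] / (12λ) = 1 − (0.3558 − 0.2123) / 0.5166 = 0.722.
- N = 277.3 / 0.722 = 384. Events per group = 192 × 0.722 = 138.6, reported as 139.
- Attrition: 384 × 1.15 = 441.6, rounded up to 442.

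The figures match, so the stated size is a pure noninferiority calculation.

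**Step 2: closed form for dilution.** SE of log HR = √(4/278) = 0.120. If the true HR is 1.4 and departures remove a fraction d of the log HR, then P(declare noninferiority) = Φ(d × ln 1.4 / SE − 1.960).

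- d = 0: Φ(−1.960) = 2.5%
- d = 0.10: HR seen 1.35; 4.7%
- d = 0.15: HR seen 1.33; 6.2%
- d = 0.20: HR seen 1.31; 8.1%

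**Step 3: simulation from departure shares.** 192 per arm; exponential RFS; hazard ln 2 / 16.1 for patients who receive TACE and 1.4 times that for those who do not; Cox model; noninferiority declared if the upper two-sided 95% limit is below 1.4; 4,000 trials per row.

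| TACE arm untreated | Follow-up arm given TACE | Mean ITT HR | False noninferiority |
|---|---|---|---|
| 0% | 0% | 1.40 | 2.5% |
| 5% | 0% | 1.38 | 4.0% |
| 10% | 0% | 1.36 | 4.5% |
| 5% | 5% | 1.35 | 4.5% |
| 10% | 10% | 1.31 | 9.4% |
| 20% | 0% | 1.31 | 8.2% |
| 20% | 20% | 1.22 | 21.8% |

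The Monte Carlo standard error near 4% is √(0.04 × 0.96 / 4000) = 0.3 percentage points, so the 4.0% and 4.5% rows are not clearly distinct. The trend is clear, and it agrees with Step 2.

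**Step 4: does it matter which arm has the 16.1-month median?** Section 2.12 gives that median for intensive follow-up, while Step 3 put it on TACE. With it on follow-up, the TACE event probability at HR 1.4 is 0.600, so events = 192 × (0.722 + 0.600) = 253.8 and SE = √(4/253.8) = 0.1255. At d = 0.10 the error is Φ(0.10 × 0.3365 / 0.1255 − 1.960) = Φ(−1.692) = 4.5%, against 4.7% in Step 2. The choice hardly matters.

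**The case against.** The strongest reply is that the declared test is superiority. Sections 2.1 and 2.13 both say so, and for that test ITT is the standard conservative set. This stands, and it makes the point conditional. A reader might infer from 2.12 that the trial's 2.5% error already fails. The documents do not support that: the 2.5% belongs to the sizing section, and no noninferiority test is specified.

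A second reply is that exposure to dilution is limited. This largely stands.

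- TACE is a single session, given at most a week after randomization, and section 2.8 describes embolization before the catheter is withdrawn. That some patients go untreated is possible but not stated.
- A reader might infer that crossover is expected. Nothing provides for it: section 2.8 gives the follow-up arm no embolic or chemotherapeutic agent, and section 2.9.4 intends participants to be blinded.
- Section 2.10 bans antitumor therapy until 120 days after the final intervention, and treatment after recurrence comes after the RFS event. The ban does, however, end well before the assumed 16.1-month median.
- Section 2.6 lists new antitumor therapy among the landmarks for ending follow-up. Where that is applied, the result is a censoring question rather than dilution. Departures balanced between arms need not move the HR towards 1.

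A third reply is that per-protocol sets are normally left to an analysis plan, which is not shown. That would answer a complaint of omission. It does not fully answer a rule covering all analyses, which a plan adding a per-protocol analysis would contradict if the sentence is read literally.

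Finally, one might infer that ITT is invalid for noninferiority, or that a per-protocol set should replace it. Neither follows. ITT preserves randomization, while a per-protocol set selects on behaviour after randomization and can be biased in either direction.

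**Conclusion.** The point holds conditionally. If the sponsor confirms that superiority is the only claim, the ITT rule in 2.7 is appropriate and this point lapses. If noninferiority is intended, as the whole of 2.12 implies, or any statement is made against 1.4, the rule as worded excludes the analysis that would show whether similar exposure produced the result.

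The plausible inflation for a one-session treatment is modest: from 2.5% to about 4.0% or 4.5% with 5% or 10% of the TACE arm untreated. It reaches about 9% only with 10% mixing in both arms. The 20% rows are a stress test and have no basis in the text. All of these results assume a true HR exactly at the margin and departure rates that the article does not give.

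**What to change.** 1. Reconcile 2.12 with 2.13 (noninferiority at one-sided 0.025 against superiority at one-sided 0.05), and state which arm is to be shown noninferior.
2. Amend the sentence in 2.7 along these lines: ITT is the primary analysis. For any claim against the 1.4 margin, a per-protocol analysis is prespecified as the key supportive analysis. Noninferiority is concluded only if the per-protocol estimate is consistent with ITT, and disagreement is reported as inconclusive.
3. Define the per-protocol set before unblinding from rules already in the protocol: eligible; allocated procedure received as described in 2.8 and within the interval in 2.9.1; no non-protocol antitumor therapy before recurrence. State in advance what counts as consistent.

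The cost is a few sentences, one further run of the same model, and a slightly more cautious noninferiority conclusion. The per-protocol set may carry selection bias, which is why it supports ITT and does not replace it. Because it is supportive, the sample size need not change. Requiring the per-protocol set itself to keep the planned size would take 442 / 0.95 = 465.3, so 466 patients, at an assumed 5% non-adherence, or 442 / 0.90 = 491.1, so 492, at 10%. Section 2.12 already cites feasibility limits, so that stricter version is not proposed here.

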### Objectives

2.1

This study is a multicenter phase III RCT, aims to rigorously evaluate the clinical efficacy of adjuvant TACE of HCC patients with high-risk recurrence factors following curative hepatectomy. The primary endpoint of this study is to investigate whether adjuvant TACE could improve RFS in high-risk HCC patients following curative hepatectomy. The key secondary endpoints include the safety and tolerability of adjuvant TACE—such as incidence of treatment-related adverse events (TRAEs) and serious adverse events (SAEs), and the rate of treatment discontinuation attributable to TRAEs or SAEs—as well as the effects of adjuvant TACE versus intensive follow-up on OS, median RFS, and time to tumor recurrence.

RFS is defined as the interval from randomization to the first imaging-confirmed recurrence of HCC—whether intrahepatic or extrahepatic—or death from any cause. TRAEs is defined as any unfavorable or unintended medical occurrences following informed consent, irrespective of causality. SAEs is defined as events that result in death, are life-threatening, require hospitalization or prolong hospitalization, result in persistent or significant disability, cause congenital anomalies, or represent other medically significant conditions. OS is defined as the time from randomization to death from any cause; time to recurrence, defined as the interval from curative hepatectomy to first imaging-confirmed recurrence.

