### Interventions

2.8

All enrolled participants will undergo hepatic arteriography 4–8 weeks following curative hepatectomy. With the patient in the supine position, standard aseptic preparation and sterile draping of the right groin will be performed. After local anesthesia with 5 mL of 2% lidocaine at the right femoral artery puncture site, a 5F arterial sheath will be inserted using the Seldinger technique. A 5F hepatic catheter will then be advanced into the celiac trunk for angiographic assessment. The hepatic arterial system, including the left and right hepatic artery branches, will be systematically evaluated to identify intrahepatic tumor staining. Detection of one or more foci of tumor staining will indicate that the initial hepatectomy did not meet criteria for curative resection, and such patients will be excluded. Participants without evidence of tumor staining will be randomly assigned to either the adjuvant TACE group or the intensive follow-up group.

In the adjuvant TACE group, superselective catheterization will be performed targeting the hepatic resection margin, followed by embolization using an emulsion of 50 mg lobaplatin and 3–5 mL ethiodized poppyseed oil. This regimen is based on prior RCTs demonstrating a reduction in postoperative HCC recurrence with adjuvant TACE.^30^^,^^31^ Polyvinyl alcohol embolic microspheres will not be utilized, as they are not part of the standard adjuvant protocol. In the intensive follow-up group, hepatic arteriography will be performed without administration of embolic or chemotherapeutic agents. Upon completion of the procedure, the catheter and arterial sheath will be removed, and manual compression will be applied to achieve hemostasis. Adjuvant TACE will be administered as a single session only.

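### Intention-to-treat is stated for all analyses with no exception for safety, so TACE toxicity would be grouped by assigned arm and its excess slightly understated

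*Protocol article*

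**What the plan says.** Section 2.7 (Strategies to improve adherence to interventions) gives the rule without qualification: "All analyses will follow the intention-to-treat principle". Section 2.1 (Objectives) brings toxicity within its reach: "The key secondary endpoints include the safety and tolerability of adjuvant TACE", measured by TRAEs, SAEs and discontinuations due to them. The only other remark on safety analysis is in section 2.6.3 (Criteria for discontinuation): "all SAEs and adverse events will remain included in safety analyses". That keeps events after a patient stops, but does not say in which group they are counted. Sections 2.13 and 2.14 name no other analysis population.

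On exposure, section 2.8 (Interventions) places randomisation after a clean angiogram ("Participants without evidence of tumor staining will be randomly assigned to either the adjuvant TACE group or the intensive follow-up group") and fixes one treatment ("Adjuvant TACE will be administered as a single session only"). Section 2.9.1 (Sequence generation) allows a gap: "The interval between randomization and administration of adjuvant TACE will not exceed 1 week".

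**The concern.** Grouping by assigned arm suits RFS and OS. For a harm endpoint it errs in the unhelpful direction, because every mismatch between assignment and exposure makes the arms look more alike.

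The article's own terms allow such mismatches. Up to a week may pass between randomisation and TACE, and consent may be withdrawn or the investigator may stop treatment in that time. With only one session, a patient who misses it has no exposure at all but still counts in the TACE denominator.

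Grouping also carries more weight here than usual. Section 2.1 defines TRAEs without regard to cause, so the between-group contrast is the main means of attributing events to TACE. The Discussion expects that TACE may add no benefit once resection is truly curative, so measured harm bears on the trial's conclusion.

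**Working it through.** The article states no figure that depends on this rule, so there is nothing to reproduce. The sample size in section 2.12 rests on RFS events and does not involve the safety grouping.

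**Does the rule reach safety?** Section 2.7 says all analyses, section 2.1 lists safety as a key secondary endpoint, and section 2.6.3 speaks only to retaining events. No text limits the rule to efficacy, so read literally it covers safety.

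**Inputs, all assumed because the article gives none:**
- p1, SAE risk with TACE: 20%.
- p0, SAE risk with angiography only: 5%.
- f, share of the TACE arm not embolised: 2% to 5%, with 10% as a stress case.
- g, share of controls given adjuvant TACE: 0, then equal to f as a stress case.
- Patients not embolised carry risk p0, and controls given TACE carry risk p1.

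**Formulas:**
- TACE arm as assigned: (1 − f) p1 + f p0
- Control arm as assigned: (1 − g) p0 + g p1
- Difference: (1 − f − g)(p1 − p0)

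Each 1% of an arm affected therefore removes 1% of the true difference, whatever p1 and p0 are.

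**Results with g = 0 (true difference 20 − 5 = 15.0 points):**
- f = 2%: 0.98 × 20 + 0.02 × 5 = 19.7%; difference 14.7 points.
- f = 5%: 0.95 × 20 + 0.05 × 5 = 19.25%; difference 14.25 points.
- f = 10%: 0.90 × 20 + 0.10 × 5 = 18.5%; difference 13.5 points.

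**Stress case with g = f:**
- 2% each: 0.96 × 15.0 = 14.4 points.
- 5% each: 0.90 × 15.0 = 13.5 points.

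With 442 / 2 = 221 patients per arm, 2% to 5% not embolised is about 4 to 11 patients.

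**How far can crossover add to this?** Four provisions narrow it and two leave it partly open.
- Patients found to have staining leave the trial: "TACE will be performed for clinical management; however, such participants will be excluded from the study".
- Section 2.10 bars antitumour therapy until 120 days after the final study intervention.
- Note o to Table 1 brings the safety visit forward to before any new antitumour therapy.
- The same note ends the SAE monitoring window at that point if it comes before 90 days.
- Against this, the discontinuation item in section 2.6.3 exempts adjuvant TACE: "initiation of antitumor therapy other than adjuvant TACE or antiviral therapy for hepatitis B or C after curative hepatectomy".
- Table 1 also marks adverse event assessment at the survival visits.

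What remains is adjuvant TACE given to a control by mistake or off protocol.

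**The case against.** **Context.** The sentence sits in a section on adherence, and the text after it concerns keeping patients in follow-up once they stop treatment. It may have been meant only as a promise not to drop non-adherers. That is a fair reading of intent, but the wording is general and a reader of the article cannot tell that safety is treated differently.

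**Unseen documents.** This is a condensed article, and a safety population is commonly defined in the full protocol or SAP. A reader might infer that the plan has no safety set; the article does not support that, and its silence is not the point. The point is that the published rule is positive and unqualified. A SAP that grouped safety by treatment received would contradict it, and a SAP that followed it would group toxicity by assignment.

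**Crossover.** A reader might infer that any TACE given to a control would count against the control arm. The documents do not support that: TACE for staining leads to exclusion, and TACE given later as new antitumour therapy falls largely outside the safety window.

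**Rarity.** Randomisation follows a clean angiogram, section 2.8 describes what reads as a single procedure, and section 2.9.4 states that participants are blinded, which makes withdrawal prompted by allocation less likely. Most of the listed reasons for discontinuation would arise after the one session. This stands: non-embolisation is possible, but nothing in the article suggests it will be frequent.

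**Conclusion.** The point holds as a minor one. The article fixes an unsuitable rule for one of its named endpoints by extending intention-to-treat to safety, and the resulting bias is toward no difference in harm. At an assumed 2% to 5% not embolised, with assumed SAE risks of 20% and 5%, the excess of 15.0 points is reported as 14.7 to 14.25. The size rests on those assumed rates and on non-embolised patients having the angiography-only risk; the direction requires only that TACE carries the higher risk.

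A reader might go further and infer that TACE toxicity would be seriously understated or the harm conclusion overturned. The documents give no rate of non-embolisation or crossover that would support this. Sample size, power and the RFS analysis are untouched. This concerns the analysis population, not clinical management.

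**What to change.** In section 2.7, limit the intention-to-treat sentence to the efficacy analyses: RFS, OS and time to recurrence. Add that TRAE and SAE analyses include the randomised patients who had angiography, grouped by treatment actually received (lobaplatin-oil emulsion versus angiography only), with a table by randomised arm as support. Check that the SAP says the same.

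The cost is a short wording change and one extra table, using procedure data the trial needs to record in any case. The drawback is that groups formed by treatment received are not exactly the randomised groups; the supporting table covers this. It is best settled before the first interim analysis, which section 2.16 plans after about 50 participants have had angiography.
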